## Abstract

**Background:**

Previous studies have shown that electroacupuncture (EA) has a significant effect on acute pain, but it has not solved the clinical problem of the chronification of acute pain. Diffuse noxious inhibitory controls (DNIC) function as a reliable indicator to predict the risk of chronic pain events. DNIC function in knee osteoarthritis (KOA) patients has been demonstrated to gradually decrease during the development of chronic pain. The purpose of this study is to conduct a randomized, controlled clinical trial to determine if EA can repair impaired DNIC function and thus prevent chronification of the acute pain of KOA.

**Methods/Design:**

This is a multicenter, single blind, randomized, controlled, three-arm, large-scale clinical trial. A total of 450 KOA patients will be randomly assigned to three groups. The strong EA group will receive EA with high-intensity current (2 mA < current < 5 mA) at the ipsilateral ‘Neixiyan’ (EX-LE5), ‘Dubi’(ST35), ‘Liangqiu’(ST34) and ‘Xuehai’ (SP10). The weak EA group will receive EA with low-intensity current (0 mA < current < 0.5 mA) on the same acupoints. The sham EA group will receive EA with low-intensity current (0 mA < current < 0.5 mA) with fine needles inserted superficially into the sites 2 cm lateral to the above acupoints. The patients will be treated with EA once a day, 30 minutes per session, in 5 sessions per week, for 2 weeks. In order to determine the best stage of KOA for effective EA intervention, patients within the treatment groups also will be divided into four stages. The primary outcomes are Visual Analog Scale (VAS), DNIC function and the Western Ontario and McMaster Universities Osteoarthritis Index (WOMAC). Clinical assessments will be evaluated at baseline (before treatment) and after 5 to 10 sessions of treatment.

**Discussion:**

This trial will be helpful in identifying whether strong EA is more effective than weak EA in reversing chronification of acute pain through repairing the impaired DNIC function and in screening for the best stage of KOA for effective EA intervention.

**Trial registration:**

Chinese Clinical Trial Registry Number: ChiCTR-ICR-14005411. The date of registration is 31 October 2014.

## Background

Knee osteoarthritis (KOA) is one of the most common types of osteoarthritis and often occurs in older adults [1]. Patients with KOA often suffer from pain around the joints and have a high risk of chronification of acute pain. Chronification of acute pain means that persistent acute pain without positive intervention can damage the nervous system and then change into intractable chronic pain [2]. In recent years, a series of clinical randomized controlled trials indicated that electroacupuncture (EA) is effective for treating various painful diseases such as KOA in the acute phase but did not solve the clinical problems of the chronification of acute pain of KOA [3].

The concept of diffuse noxious inhibitory controls (DNIC) has attracted particular attention in the past decades, which means under normal conditions, pain can be attenuated by a conditioning noxious stimulus to a remote body region [4]. DNIC function is now regarded as a reliable indicator for predicting the risk of chronic pain [5,6]. DNIC function in KOA patients has been shown to gradually decrease with the development of chronic pain [7]. Thus, we hypothesized that the process of chronification of acute pain may be related to gradually impaired DNIC function, and EA may prevent the occurrence of chronification of acute pain by improving DNIC function.

The aim of this study is to explore whether EA can reverse impaired DNIC function by reducing the pain of KOA during the process of chronification of acute pain. Moreover, we will screen for the best EA therapeutic regimen, which will include optimizing the intensity of the current used in the EA stimulation and determining the best stage for effective EA intervention using a randomized controlled clinical trial.

## Methods/Design

### Ethics

The study is in accordance with the Declaration of Helsinki, it has been approved by the Chinese Ethics Committee of Registering Clinical Trials (reference: ChiECRCT-20140035), and it also has been registered with Chinese Clinical Trial Registry (ChiCTR-ICR-14005411). Before randomization, all patients will be expected to sign a written informed consent.

### Design

A randomized, controlled, three-arm, large-scale trial to compare two true EA groups (strong EA and weak EA) with a sham EA group will be undertaken in this study [8]. Four hundred and fifty KOA patients will be recruited from the following six hospitals: the Combined Traditional Chinese and Western Medicine Hospital Affiliated to Huazhong University of Science and Technology, The Third Hospital of Wuhan, Central Hospital of Wuhan, Union Hospital Affiliated to Tongji Medical College of Huazhong University of Science and Technology, Wuhan Hospital of Traditional Chinese Medicine, and The Fifth Hospital of Wuhan. Patients will be randomized in a ratio of 1:1:1 to the strong EA group, weak EA group and sham EA group. After submitting informed consent and being randomized, patients will receive 10 sessions of EA treatment over a period of 2 weeks, with a treatment frequency of 5 sessions per week. Each session will last 30 minutes. Patients will be asked to accept assessments at baseline, as well as at the end of the first and second weeks of the treatment phase. Time points and groups are shown in Figure 1.

**Figure 1 Fig1:**
[figure not shown]
**Trial flow chart.**

### Randomization and blinding

Patients who meet the inclusion criteria will be randomly assigned to one of three groups (strong EA, weak EA or sham EA) in a ratio of 1:1:1 using a computer-generated random allocation sequence through the stratified block randomization method of SAS version 9.1.3 (SAS Institute Inc., USA). The randomization will be performed by an independent research assistant, who will inform the acupuncturists of the treatment assignments by mobile message. Allocation concealment will not be exposed until the final data analysis report is completed.

To maintain blinding, each patient will have needles (true or sham) inserted into his/her ipsilateral leg. The needles are connected to an EA apparatus, and the patients can feel electric stimulation. Strong and weak EA groups will be acupunctured on four acupoints. The sham EA group will be acupunctured on four non-acupoints without ‘De-qi’.

In this clinical trial process, the patients, statisticians and the evaluators for the statistical data and outcomes are blind to the treatment allocation. However, the blind method is not used by acupuncturists in the implementation of EA manipulation because it is not feasible to conceal allocation from them.

### Patients

#### Study population

Patients will be recruited from among acupuncture inpatients and clinics of six hospitals with a target sample size of 450 subjects. The trial will be ongoing from September 2014 to September 2016.

#### Inclusion criteria

Patients who meet the clinical criteria for KOA formulated by the American College of Rheumatology (ACR) will be considered for inclusion [9]. According to the ACR, clinical KOA is defined as knee pain and at least three out of seven of the following criteria: patient is older than 50 years of age, morning stiffness lasts less than 30 minutes, crepitus is present, bony enlargement is apparent, bony tenderness is present, no palpable warmth is present, and presentation is suggestive of a radiological osteophyte.

#### Exclusion criteria

The exclusion criteria are as follows:Patient has had an adverse reaction to acupuncture or is unwilling to accept acupuncture treatment.Patient conforms to the inclusion criteria, but does not follow prescribed treatment, which decreases the curative effects of EA so that it cannot be judged, or patient has incomplete information that may interfere with his/her ability to accurately judge the effects of his/her treatment.Patient has accompanying severe cardiovascular, cerebral, hepatic, renal, or hemopoietic diseases [10].Patient has inflammatory arthritis such as rheumatoid arthritis, gouty arthritis, *etcetera* or other diseases that may affect the condition of the knees [11].Patient is pregnant, attempting to become pregnant or lactating [10].Patient has a mental disease [11].

#### Recruitment of patients

Two schemes will be used to recruit patients with KOA. The first is to recruit patients in the outpatient and inpatient departments from the six hospitals. The chief physicians of the acupuncture and rehabilitation department in each hospital will screen eligible patients according to the inclusion/exclusion criteria with the help of research assistants. Moreover, potential patients in local communities and out-hospital clinics will be recruited by advertisements through posters, leaflets, newspapers, and so on. After being screened and found to meet the inclusion criteria, the patients will be included only if they agree to join in every procedure of the trial willingly and provide written informed consent.

### Interventions

#### Electroacupuncture group

According to the Traditional Chinese Medicine meridian theory of treating pain of KOA [11,12], patients in the strong and weak EA treatment groups will be treated with EA on ipsilateral acupoints of ‘Neixiyan’ (EX-LE5), ‘Dubi’(ST35), ‘Liangqiu’(ST34) and ‘Xuehai’ (SP10) once a day (Figure 2). The sterile, disposable Hwato needles used in this trial are made in Suzhou, China. Patients are positioned on the bed, supported by two pillows under the knees and instructed to assume a comfortable position and not to move during the 30-minutes stimulation period.

**Figure 2 Fig2:**
[figure not shown]
**The points used in the trial.** The lines refer to acupoints of ‘Liangqiu’ (ST34) and ‘Dubi’ (ST35) on the lateral side of the knee, and ‘Xuehai’ (SP10) and ‘Neixiyan’ (EX-LE5) on the medial side of the knee. The points lateral to the above four acupoints refer to non-acupoints.

After the local area has been disinfected, the needles (30-gauge with an outer diameter of 0.32 mm and a length of 50 mm) will be inserted at a depth of 25 to 40 mm vertically and ‘De-qi’ (the acupuncture sensation of fullness, heaviness, dull aching or warmth) sensation will be achieved in the strong and weak EA groups through lifting and thrusting combined with twirling and rotating the needles. Direct current and continuous wave will be delivered with a medical EA apparatus (model G9805, Shanghai, China), at 2 Hz frequency and 0.5 ms pulse width for 30 minutes. EX-LE5 will be connected to ST35, and SP10 will be connected to ST34 with a pair of electrodes [10,13]. Different stimulation intensities will be allocated to the strong EA and weak EA groups. The strong EA group will receive the maximum tolerable intensity of current (2 mA < current < 5 mA). However, patients in the weak EA group will receive low-intensity current (0 mA < current < 0.5 mA), and they will be instructed to ask the doctor to stop the increase in intensity when the sensations of current occur. After the intervention period, all needles and the EA apparatus will be removed (Table 1).

**Table 1 Tab1:** **Details of each group**

**Group**	**Acupoints**	**Stimulation parameters**
Strong EA group	Neixiyan	Direct current, continuous wave, at 2 Hz frequency and with 0.5 ms pulse width for 30 minutes. Maximum tolerable intensity of current will be delivered, 2 mA < current < 5 mA. EX-LE5 will be connected to ST35 and SP10 will be connected to ST34 with a pair of electrodes.
	(EX-LE5)	
	Dubi (ST35)	
	Liangqiu (ST34)	
	Xuehai (SP10)	
Weak EA group	Neixiyan	Stimulation indexes and acupoint’ connections are the same as in the strong EA group, but the patients will just feel the sensations of current, 0 mA < current <0.5 mA.
	(EX-LE5)	
	Dubi (ST35)	
	Liangqiu (ST34)	
	Xuehai (SP10)	
Sham EA group	The sites are 2 cm lateral to the above	Fine needles will be inserted superficially into the sites 2 cm lateral to the above four points with low-intensity current as same as in the weak EA group.
	four points	

Note: EA, electroacupuncture.

#### Sham EA group

In the sham EA group, a sterile, disposable, fine and short needle (35-gauge needle with an outer diameter of 0.20 mm and a length of 25 mm) will be used and inserted superficially (to an approximate depth of 5 to 10 mm) into the sites of the non-acupoints 2 cm lateral to the above four acupoints (Figure 2). However, the ‘De-qi’ sensation will not be intentionally elicited in this group. Electrical stimulation will be delivered with low-intensity current (0 mA < current < 0.5 mA) at 2 Hz frequency and 0.5 ms pulse width for 30 minutes, which is the same as for the weak EA group (Table 1).

#### Education of practitioners

All EA and sham EA treatments will be performed by acupuncturists who have been qualified for at least 3 years and hold Chinese medicine practitioner licenses from the Ministry of Health of the Peoples Republic of China. Each acupuncturist will take a pretrial training course for this clinical study. The chief physicians will train all acupuncturists and observe their techniques periodically to ensure standardization. In addition, all study protocols and details, including the recording method for the case report form, outcome assessment methods, and monitoring process, will be standardized among the six centers by the research assistants.

### Outcome assessments

#### Primary outcome measurements

The primary outcome measurements are the Visual Analog Scale (VAS), DNIC function and the Western Ontario and McMaster Universities Osteoarthritis Index (WOMAC).

VAS is an internationally recognized pain scale. It is a 100-mm line ranging from 0 (no pain) to 100 (pain as bad as it could be) [14].

The prediction of chronification of acute pain can be indicated by DNIC function, which means that pain elicited by a noxious stimulus applied to a given body site can be attenuated by application of a conditioning noxious stimulation to another, even distant body region [15]. DNIC function will be measured according to the procedure shown in Figure 3. On the Ashi-point (pain spot) of the affected knee, the research assistant will apply a 180-g von Frey filament (bending it so that it forms a 45-degrees angle with the skin) three to five times within a 1-cm-diameter circle (Figure 3A). The patients will be asked to rate the intensity of pain as VAS1 [5], which is the induced mechanical pain score of the affected knee. Then, the patients will be asked to immerse the contralateral hand, including the wrist, into nociceptive cold water (10 to 12°C) for 1 minute and rate the intensity of the pain induced by the 180-g von Frey filament on the Ashi-point as VAS2 (Figure 3B). For healthy people, the conditioning cold noxious stimulation can activate the descending inhibitory system of the spinal cord. VAS2 is used to detect the induced mechanical pain score of the affected knee after conditioning with the cold noxious stimulation on the contralateral hand. Finally, DNIC function will be assessed by measuring the difference in pain ratings before and after immersion (DNIC = (VAS1-VAS2)/VAS1). Thus, the decreased ratio in pain scores of the affected knee before and after the cold noxious stimulation of the hand is the DNIC function [2,16].

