### Data analysis

Data with normal distribution will be presented as means ± SEM. We will use a one-way analysis of variance (ANOVA) or a two-way ANOVA to determine the overall effect of EA. The Post hoc test (Newman Keuls test) will then be used to determine the statistical differences among individual groups. A *P* value of less than 0.05 will be considered statistically significant. Data showing an abnormal distribution will be analyzed by the Wilcoxon signed-rank test.

In order to determine which EA intervention is the best for each of the different stages of KOA, patients in the three EA groups will be further divided according to four different stages of KOA:The acute pain stage group. The pain of KOA has been ongoing for less than 6 months.The early chronic pain stage group. The pain of KOA has been ongoing for 6 months to 3 years.The medium-term chronic pain stage group. The pain of KOA has been ongoing for 3 to 5 years.The advanced chronic pain stage group. The pain of KOA has been ongoing for more than 5 years (Figure 4A).

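### Three unranked primary outcomes and no primary visit, all at P < 0.05: if any one counts as success, the false-positive rate is about 10–14%, or 14–23% if both visits are tested, not 5%

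*Protocol article*

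**What the plan says.** All references are to the protocol article.

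- **Primary outcome measurements:** "The primary outcome measurements are the Visual Analog Scale (VAS), DNIC function and the Western Ontario and McMaster Universities Osteoarthritis Index (WOMAC"). There is no order among the three and no rule on whether one, some or all must be significant.
- **Design:** "Patients will be asked to accept assessments at baseline, as well as at the end of the first and second weeks of the treatment phase". Neither post-baseline visit is called primary. The Abstract describes the timing as "after 5 to 10 sessions of treatment".
- **Data analysis:** "We will use a one-way analysis of variance (ANOVA) or a two-way ANOVA to determine the overall effect of EA". The second factor of the two-way model is not named. Newman-Keuls then separates the individual groups. One threshold applies throughout: "A *P* value of less than 0.05 will be considered statistically significant".
- **Sample size:** 150 patients per group, at a 5% level with 90% power and 15% attrition. The calculation uses DNIC only (assumed increases of 30%, 20% and 15% for strong, weak and sham EA).

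**The concern.** The sample size paragraph sets a 5% level, but that level describes one test. The protocol declares three primary outcomes of equal standing and gives each the same unadjusted threshold. It leaves two visits at which each could be tested. Newman-Keuls deals with the three arms within one analysis and does nothing across outcomes or visits.

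Followed as written, a significant VAS result alone would rank equally with a significant DNIC result, although the aim and the Discussion centre on DNIC. A trial in which EA has no effect on anything would then have well over a 5% chance of being reported as positive on a primary outcome. This goes beyond detail left to an analysis plan, because the protocol itself fixes the three primaries and the threshold.

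**Working it through.** **The plan's own figure.** The 150 per group cannot be reproduced, because the DNIC increase is described as an average and no standard deviation is given. With 150 × 0.85 ≈ 127 completers per arm, 90% power for a three-group ANOVA on means of 30, 20 and 15 implies a standard deviation of about 34 percentage points. The check below does not depend on this.

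**Inputs from the protocol.** Three primary outcomes, two post-baseline visits, threshold 0.05 per test, three arms at 1:1:1.

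**Inputs assumed.** Correlation between outcomes 0.3–0.8 and between visits 0.6–0.9; the protocol gives neither. Success means a significant overall group test on any primary outcome, and no arm truly differs on any of them.

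**Step 1: independent tests (upper limits).** The chance of at least one false positive in *k* tests is 1 − (1 − 0.05)^*k*.

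- *k* = 3 (one test per outcome): 1 − 0.95³ = 14.3%.
- *k* = 6 (each outcome at both visits): 1 − 0.95⁶ = 26.5%.

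**Step 2: correlated tests.** Simulation of overall three-group tests (2 degrees of freedom, large-sample form, 400,000 replicates per setting, with equal correlation among the outcomes):

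| Correlation between outcomes | 3 tests, one visit | 6 tests, visits 0.6 | 6 tests, visits 0.7 | 6 tests, visits 0.8 | 6 tests, visits 0.9 |
|---|---|---|---|---|---|
| 0.3 | 13.7% | 23.3% | 22.2% | 21.2% | 18.9% |
| 0.5 | 12.8% | 21.7% | 20.7% | 19.4% | 17.5% |
| 0.7 | 11.1% | 19.0% | 18.1% | 17.1% | 15.4% |
| 0.8 | 10.0% | 17.2% | 16.5% | 15.4% | 14.0% |

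Three tests therefore give about 10–14%, and six give about 14–23%.

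**Step 3: which count applies.** Separate one-way ANOVAs at each visit give six tests. A two-way model with group and time gives two group-related tests per outcome (main effect and interaction), so again about six. A single group test per outcome gives three. The Data analysis section does not say which is meant. Newman-Keuls holds the error rate across the three arms within one analysis, so the pairwise comparisons add nothing to the count. The analyses by disease stage are not counted here.

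**Step 4: what a correction would cost.** Bonferroni over three tests uses 0.05/3 = 0.0167 each, with an overall rate of 1 − (1 − 0.0167)³ = 4.9% if independent. For a test with 90% power at two-sided 0.05, power becomes Φ(1.960 + 1.282 − 2.394) = Φ(0.848) ≈ 80%. The same calculation for the three-group F test with 127 per arm also gives 80%. Over six tests (0.0083 each) power is about 73%.

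**The case against.** **Six tests are not stated.** A reader might infer that each outcome is tested separately at each visit and quote about 20–26% as the trial's error rate. The documents do not support that as fact. The Data analysis section speaks only of an overall effect of EA, and the unnamed second factor could be time or disease stage. The 26.5% also needs independence, which is not credible for the same outcome in the same patients one week apart. This objection stands, and it is why the three-test range is given first.

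**All three might be required.** That rule would remove the inflation, but it appears nowhere. The Discussion points away from it: it lists VAS and WOMAC with the secondary measures as showing pain relief that both EA intensities may produce, and reserves the distinguishing hypothesis for DNIC. That passage shows DNIC is the natural lead outcome, but it sets no formal hierarchy.

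**This is a condensed article.** The analysis plan is not at hand and Figure 1, which shows time points, is not reproduced. An adjustment or a primary visit could be stated elsewhere. Absence alone would be no finding; what remains is that the protocol affirmatively names three equal primaries with one flat threshold.

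**The Abstract wording.** A reader might infer from "after 5 to 10 sessions of treatment" that the assessment time is open. It is only a wording slip. The Design section fixes assessments at the end of weeks 1 and 2, with five sessions per week, so after sessions 5 and 10.

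**Conclusion.** The concern holds in a bounded form. If any one primary outcome can carry the trial, the stated rules give a false-positive rate above the 5% in the sample size paragraph under every test structure considered:

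- about 10–14% with one test per outcome (14.3% if independent);
- about 14–23% if each outcome is tested at both visits (26.5% only under independence).

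The low end is still twice the stated level. The ranges depend on the assumed correlations and on no arm differing on any primary outcome. They would not apply if all three outcomes had to be significant, or if a document not shown specifies an adjustment. The protocol as published states neither.

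**What to change.** **Preferred change.** Name DNIC at the end of week 2 (after session 10) as the single primary analysis. It is the only outcome with a sample size basis, it carries the main hypothesis, and week 2 completes the treatment course. Test VAS and WOMAC at week 2 as key secondary outcomes, in fixed order or by Holm, only if DNIC is significant. Treat week 1 as supportive. This restores 5% for the primary claim with no change in sample size.

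**If all three must stay primary.** Use Holm or Bonferroni across the three at week 2 and restate the power. Under Bonferroni at the planned size it is about 80% per test, if it was 90% at 0.05. That figure speaks only to DNIC, since VAS and WOMAC were not sized.

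**Wording.** Align the Abstract with the Design section: assessments after 5 and 10 sessions.

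**Cost.** A result positive only on VAS or WOMAC is no longer an unadjusted primary success. Recruitment has begun, so the change must be registered as a dated amendment. The Randomization and blinding section keeps allocation concealed until the final analysis report is complete, so it can still be made without sight of results by arm.

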### Sample size

According to a previous study and our pilot data, the sample size calculation assumed an average DNIC increase percentage of 30% for the strong EA group [19]. The DNIC increase percentage for the weak EA group and sham EA group are assumed to be 20% and 15%, respectively. It is assumed that 15% of the trial patients will be lost to attrition. With this scenario, 150 patients need to be allocated to each treatment group to establish a difference among the treatments at a 5% level and with a power of 90% [20].

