To screen for the optimal intensity of EA for improving DNIC function, the effect of strong EA and weak EA will be compared. EA with low-intensity current (less than 1 mA) has been demonstrated to mainly excite large fibers (Aβ fiber), which may not activate the DNIC function [28]. Instead, this innocuous stimulation may only exert an analgesic effect through the spinal mechanism of gate control theory [29]. In contrast, EA with high-intensity current (more than 2 mA) excited thin fibers (A δ and/or C fibers) and may activate DNIC function [30]. Thus, we will compare the effect of strong EA and weak EA on repairing impaired DNIC function to screen for the best EA intensity to prevent chronification of the acute pain of KOA. We hypothesize that both strong EA and weak EA may have some pain-reducing and inflammation-relieving effects, which will be assessed with VAS, WOMAC, NRS, ES, PPI and ROM. However, strong EA may be more effective in improving DNIC function and, thus, in reversing the chronification of acute pain [28].

Moreover, we also will try to determine the best stage of KOA for EA intervention. DNIC function is the function of the endogenous analgesic system [16]. In other words, the process of gradually decreased DNIC function is also the process of transforming acute pain to chronic pain. In this process, if patients receive EA intervention as soon as possible, it is possible that the chronification of pain in KOA patients will be prevented. However, at the later stages of chronic pain, peripheral and central sensitization will likely irreversibly damage the endogenous analgesic system function and completely impair DNIC function [2]. At that point, EA may not be as effective. So, we will further divide the KOA patients according to the stage of the disease. We hope to find the best stage for the use of EA to reverse the impaired DNIC function and prevent the chronification of acute pain.

This project will not only increase knowledge on the effects of treating KOA with EA, but also may contribute a solution to the difficult problem of the chronification of acute pain, and promote the clinical application of EA analgesia.

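### The primary DNIC ratio divides by evoked pain at the treated knee, so at follow-up it can mix DNIC change with local analgesia (direction unknown) and is unstable or undefined at low VAS1

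*Protocol article*

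**What the plan says.** DNIC function is one of three primary outcomes. The protocol article, Primary outcome measurements, defines it: "DNIC function will be assessed by measuring the difference in pain ratings before and after immersion (DNIC = (VAS1-VAS2)/VAS1"; the Figure 3 legend repeats the formula.

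- VAS1 is the response to a fixed 180-g filament at the painful spot, "which is the induced mechanical pain score of the affected knee". It is not the clinical knee-pain VAS, which is a separate primary outcome.
- For the second rating, "VAS2 is used to detect the induced mechanical pain score of the affected knee after conditioning with the cold noxious stimulation".
- The scale includes zero: "It is a 100-mm line ranging from 0 (no pain) to 100 (pain as bad as it could be". The inclusion criteria require knee pain but state no minimum evoked score.
- On timing (Design): "Patients will be asked to accept assessments at baseline, as well as at the end of the first and second weeks of the treatment phase". The follow-up denominator is therefore rated after treatment has begun. Under Interventions, the needles of both true EA arms go into points around the same knee.
- The Discussion expects that "both strong EA and weak EA may have some pain-reducing and inflammation-relieving effects", with strong EA perhaps better at improving DNIC.
- The Sample size section plans on "an average DNIC increase percentage of 30% for the strong EA group", with 20% for weak and 15% for sham EA. It does not say whether these are ratio points or percent change of the ratio.
- The Data analysis section names one-way or two-way ANOVA, with no baseline covariate.

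**The concern.** The trial's scientific claim rests on separating two things: pain relief, which the authors allow for in both true EA arms, and repair of descending inhibition, which they expect mainly from strong EA. The outcome meant to separate them is divided by a pain rating at the treated site. If the arms differ in how far they lower evoked knee pain, the ratio may differ between arms with no difference in the conditioning effect, or a real difference may be hidden.

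The formula also behaves worst where treatment works best. As VAS1 shrinks, ordinary rating error is magnified, and at VAS1 = 0 there is no score. Patients whose evoked pain has gone would need to be imputed or left out, possibly in unequal numbers across arms.

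**Working it through.** **Inputs.** From the article: the formula, the 0 to 100 mm scale, the assessment times and the planned 30%, 20% and 15%. It gives no VAS1 distribution, rating error or SD of DNIC, so all VAS values below are assumptions. The 150 per group cannot be reproduced without an SD, and this point does not depend on it.

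**Algebra.** Write D = (VAS1 - VAS2)/VAS1 = 1 - VAS2/VAS1.

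- Additive relief (c mm off both ratings): D becomes (VAS1 - VAS2)/(VAS1 - c), and the mm drop is unchanged. D rises if VAS1 > VAS2, and becomes more negative if VAS2 > VAS1.
- Proportional relief (both ratings times k): D is unchanged, and the mm drop becomes k(VAS1 - VAS2).

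**Worked patients (assumed).**

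| Situation | VAS1/VAS2 (mm) | Drop (mm) | D |
|---|---|---|---|
| Baseline | 50/40 | 10 | 10/50 = 0.20 |
| Additive, 10 mm | 40/30 | 10 | 10/40 = 0.25 |
| Additive, 20 mm | 30/20 | 10 | 10/30 = 0.33 |
| Proportional, k = 0.6 | 30/24 | 6 | 6/30 = 0.20 |
| No inhibition at baseline | 50/55 | -5 | -5/50 = -0.10 |
| Same patient, additive, 20 mm | 30/35 | -5 | -5/30 = -0.17 |
| Evoked pain abolished | 0/VAS2 | -VAS2 | undefined |

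**Instability.** A 5-mm error in VAS2 moves D by 5/50 = 0.10 at VAS1 = 50, but by 5/10 = 0.50 at VAS1 = 10.

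**Simulation 1** (assumed VAS1 ~ N(50, 20), inhibition 10 ± 10 mm, no rating error, ratings clipped to 0-100 and rounded to mm). Mean VAS1 is lowered from about 50 to 30.

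| | Mean D | SD of D | Undefined | Mean drop (mm) |
|---|---|---|---|---|
| No relief | 0.23 | 0.30 | 0.7% | 9.7 |
| Additive | 0.34 | about 0.5 | 7.0% | 8.3 |
| Proportional | 0.23 | 0.29 | 0.7% | 5.8 |

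**Simulation 2** (assumed mean VAS1 60, between-patient SD 15, true D 0.20 throughout, independent rating error on each score). Mean VAS1 is lowered from 60 to 30.

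| Error SD | Relief | Mean D | SD of D | Undefined at mean VAS1 = 30 |
|---|---|---|---|---|
| 5 mm | Additive | 0.19 to 0.41 | 0.13 to 0.36 | 3.1% |
| 5 mm | Proportional | 0.19 to 0.16 | 0.13 to 0.34 | 0.05% |
| 10 mm | Additive | 0.16 to 0.27 | 0.37 to 1.04 | 5.1% |
| 10 mm | Proportional | 0.16 to 0.01 | 0.37 to 1.25 | 0.9% |

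Under proportional relief the median stays at about 0.20 while the mean falls, because small denominators create a long negative tail. With rating error, the SD grows under either model.

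**Against the planned effects.** The planned gaps are 30 - 20 = 10, 20 - 15 = 5 and 30 - 15 = 15. Read as ratio points, additive relief of 10 or 20 mm in the worked patient adds 5 or 13 points. Read as percent change, it adds 0.05/0.20 = 25% or 0.133/0.20 = 67%. Only a between-arm difference in relief of that size would produce a between-arm artefact of that size.

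**Percent change of the ratio.** It is undefined when baseline D is 0. With a negative baseline the sign flips: going from -0.10 to +0.10 gives 0.20/(-0.10) = -200% for an improvement. The Discussion says that late-stage sensitization will likely "irreversibly damage the endogenous analgesic system function and completely impair DNIC function", so baseline values near zero are plausible.

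**The case against.** The strongest reply is that the ratio is a deliberate choice of construct. The article defines DNIC function as the proportional fall in pain; on that definition a 10-mm drop from 30 is more inhibition than a 10-mm drop from 50. Dividing by VAS1 is exactly what removes proportional relief. The absolute difference has the mirror-image fault: with proportional relief it falls from 9.7 to 5.8 mm in Simulation 1 although the inhibited proportion is unchanged, and a patient at VAS1 = 0 is scored as having zero or negative inhibition. All of this stands, and it rules out replacing the ratio by the absolute drop as sole primary measure.

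Stronger readings are tempting but not supported:

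- *The ratio rises whenever EA relieves local pain.* False under proportional relief, and false for patients with VAS2 above VAS1.
- *The bias favours the arm with most analgesia.* The article gives no size of relief by arm and no model of relief. With rating error the mean can fall in that arm.
- *The plan has no rule for VAS1 = 0 and will lose its best responders.* Such a rule may sit in an analysis plan that is not shown, so its absence is no finding. What is fixed in the article is a formula with no value there.
- *Negative baseline scores are expected.* The Discussion speaks of likely complete impairment, which suggests values near zero, not below it.

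The reply does not remove the core difficulty: a single ratio cannot show whether its change came from the conditioning effect or from the denominator.

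**Conclusion.** The concern holds in limited form. The stated primary DNIC score can be confounded with direct analgesia at the treated knee, becomes unstable as VAS1 falls, and is undefined at VAS1 = 0. The possible shift is as large as the effects the trial plans to detect: under assumed additive relief of 20 mm, 13 points in the worked patient and 11 points (0.23 to 0.34) in Simulation 1, against a planned strong-weak gap of 10 if the planning percentages are ratio points. Under proportional relief the shift is nil without rating error and downward in the mean with it. That the denominator is a post-treatment rating and that the formula fails at zero follow from the text. The sizes rest on the assumed VAS values, and the direction cannot be settled from the article.

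**What to change.** Keep the ratio as defined and add the following before analysis:

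1. Pre-specify beside it the absolute inhibition VAS1 - VAS2 in mm at week 2, defined for every patient with both ratings. Analyse it by ANCOVA with baseline inhibition and baseline VAS1 as covariates instead of unadjusted ANOVA.
2. Analyse the ratio with its own baseline value as a covariate.
3. Attribute a between-arm difference to DNIC repair only if both measures agree. If they disagree, report that local analgesia cannot be excluded as the explanation.
4. Report the number of patients with VAS1 = 0 per arm and visit.
5. State that the planning percentages in the Sample size section are differences in ratio points, and do not use percent change of the ratio.

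Both ratings are already collected, so the change is to wording and analysis only. The price is one extra analysis and a more cautious claim: if relief is proportional, the absolute measure is biased against the arm with more relief, so requiring agreement may withhold a claim of DNIC repair that is true. Adjusting for baseline VAS1 improves precision but does not correct for the post-treatment VAS1, so the agreement rule is still needed.
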